## Abstract

**Background:**

Home-based renal replacement therapy (RRT) [peritoneal dialysis (PD) and home hemodialysis (HHD)] offers independent quality of life and clinical advantages compared to conventional in-center hemodialysis. However, follow-up may be less complete for home dialysis patients following a change in care settings such as post hospitalization. We aim to implement a Home Dialysis Virtual Ward (HDVW) strategy, which is targeted to minimize gaps of care.

**Methods/design:**

The HDVW Pilot Study will enroll consecutive PD and HHD patients who fulfilled any one of our inclusion criteria: 1. following discharge from hospital, 2. after interventional procedure(s), 3. prescription of anti-microbial agents, or 4. following completion of home dialysis training. Clinician-led telephone interviews are performed weekly for 2 weeks until VW discharge. Case-mix (modified Charlson Comorbidity Index), symptoms (the modified Edmonton Symptom Assessment Scale) and patient satisfaction are assessed serially. The number of VW interventions relating to eight pre-specified domains will be measured. Adverse events such as re-hospitalization and health-services utilization will be ascertained through telephone follow-up after discharge from the VW at 2, 4, 12 weeks. The VW re-hospitalization rate will be compared with a contemporary cohort (matched for age, gender, renal replacement therapy and co-morbidities). Our protocol has been approved by research ethics board (UHN: 12-5397-AE). Written informed consent for participation in the study will be obtained from participants.

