## Methods/design

### The virtual ward intervention

The home dialysis VW protocol, tools, and evaluation system was developed through an adaptive design process. The members of the VW design team include a physician, pharmacist, dietician, home dialysis nurse, and social worker. Our protocol has been approved by research ethics board (UHN: 12-5397-AE). Written informed consent for participation in the study will be obtained from participants.

The VW intervention consists of a scheduled once to thrice - weekly physician or nurse telephone-administered standardized patient assessment tool. This tool was developed through iterative steps based on input from nephrologists (MS and CC), home dialysis nurses, and renal dieticians. The tool was vetted through dedicated nephrology divisional rounds at the University of Toronto. Feedback from academic nephrologists as well as allied health care staff was incorporated into the final version.

The standardized patient assessment tool serves as a data collection, and clinical form. Relevant domains are identified including: 1. Indication for admission to the VW; 2. Dialysis prescription; 3. Demographic and comorbidity data; 4. Medication reconciliation and 5. Symptom assessment.

The VW nephrologist admits patients and administers the standardized patient assessment tool over the telephone during scheduled VW appointments. Subsequent use of the tool proceeds 1–3 times per week by a member of the team. Patients are admitted to the VW for a planned duration of 14 days and discharged at the discretion of the health team.

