### Secondary outcomes

Our secondary outcomes will include:

1. Within subject differences in symptoms score at baseline and at discharge of VW.

2. Number of re-hospitalizations

3. Rate of re-hospitalization

4. Patient satisfaction

5. Patient encounter time (per VW admission)

6. Stratification of care gaps which are associated with re-hospitalization

7. The VW re-hospitalization rate will be compared to the hospitalization rate of a contemporary cohort (matched for age, gender, renal replacement therapy and co-morbidities).

Admission to the VW will be described in absolute terms and expressed as proportion of total patients admitted per week. Travel time to home dialysis unit and whether the dialysis is performed independently or dependently is ascertained from the patient and/or primary nurse. Dialysis independency is defined as self-reliance on the following three domains: dialysis setup and equipment maintenance, cannulation or catheter access, and dialysis therapy management.

Identification of gaps in care will be assessed by measuring discrepancies between prescribed versus delivered management strategies documented at entry to the VW. Gaps in care will be categorized as 1. Changes to dialysis prescription; 2. Coordination of care; 3. Medication changes; and 4. Symptoms management. The percentage of VW patients with identifiable gaps in care and the types of gaps will be described. We will also stratify the types of care gaps which are associated with re-hospitalization.

Rates of hospital re-admission, un-scheduled home dialysis unit, emergency room, and in-center backup visits will be recorded prospectively for a planned 3-month period and expressed as health-services utilization rates per patient-year. Re-hospitalization rates will be compared before and after the intervention within each home dialysis program.

VW re-hospitalization rate will be compared to the hospitalization rate of a contemporary incident ESRD patient cohort through an existing collaborative effort by Oliver et al. [25]. The cohorts will be matched for age, gender, renal replacement therapy and co-morbidities (Figure 1).

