### Implementation

The HDVW project will be implemented in a Vanguard fashion. A 3 month feasibility phase will be used to enroll 20 consecutive home dialysis patients at the University Health Network. Once the pilot phase of the project is achieved, enrollment from the other sites will begin with a cumulative enrollment target of 200 home dialysis patients during a 9-month period. Our target is based on previous published work in which 400 consecutive general internal medicine patients had 76 adverse events during the 2 weeks following hospital discharge. Of these adverse events, 62% were deemed either preventable or ameliorable [17]. Given that patients with ESRD are more complex than general internal medicine patients, we would estimate conservatively that our cohort would encounter a minimum of 40 events of which the majority may be preventable or ameliorable.

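### The only dated follow-up for re-hospitalization and service use starts at VW discharge, and no origin is stated for the rates, so events during the 14-day VW stay are not clearly covered

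*Protocol article*

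**What the plan says.** The abstract (Methods/design) states that re-hospitalization and service use "will be ascertained through telephone follow-up after discharge from the VW at 2, 4, 12 weeks". No other dates for collecting these outcomes appear in the article.

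The starting point of that schedule is defined under The virtual ward intervention: "Patients are admitted to the VW for a planned duration of 14 days and discharged at the discretion of the health team".

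Under Secondary outcomes, re-admissions and unscheduled, emergency and backup visits "will be recorded prospectively for a planned 3-month period and expressed as health-services utilization rates per patient-year". That sentence does not say when the 3 months begin. The same section plans a before/after comparison of re-hospitalization rates within each program, and a comparison with a matched contemporary cohort of incident ESRD patients. It states no origin for either comparison.

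Patients are in contact with the team during the stay. The abstract says "Clinician-led telephone interviews are performed weekly for 2 weeks until VW discharge"; the main text says "Subsequent use of the tool proceeds 1–3 times per week by a member of the team". The content of the tool is listed as "Relevant domains are identified including: 1. Indication for admission to the VW; 2. Dialysis prescription; 3. Demographic and comorbidity data; 4. Medication reconciliation and 5." (the fifth and last item covers symptoms). Hospitalization and service use are not in that list.

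Under Implementation, the target sample is justified by published work in which "400 consecutive general internal medicine patients had 76 adverse events during the 2 weeks following hospital discharge".

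**The concern.** A rate per patient-year needs a stated time zero, an end, and a rule for which events and which person-time count. The one origin the article attaches to follow-up is VW discharge. That point falls after entry, varies between patients, and is chosen by the people delivering the intervention.

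The article's rationale is that the transition period is one of heightened vulnerability and that the VW acts during it. A rate that starts when the VW ends would leave out the period in which an effect is most expected. No rule says how a patient re-hospitalized on, say, day 5 of the stay is counted. On leaving hospital that patient meets the first admission criterion again, so the same event could be an outcome, a new entry, or both.

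The two planned comparisons are where this matters most. If the VW rate and a comparator rate start at different distances from the qualifying event, part of any difference between them comes from the clock.

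**Working it through.** **Inputs.** Planned stay of 14 days (The virtual ward intervention). Last call 12 weeks, or 84 days, after VW discharge (abstract). Target of 200 patients: "cumulative enrollment target of 200 home dialysis patients during a 9-month period" (Implementation). Sizing rate of 76 events in 400 patients over 2 weeks (Implementation).

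**1. The article's own event figure.** 76/400 = 0.19, and 200 × 0.19 = 38. The article states a minimum of 40, describing its patients as more complex than the source population. The figure reproduces approximately. No power calculation is given, so there is none to check.

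**2. Length of the windows for 200 patients.**
- Stay: 200 × 14/365.25 = 7.7 patient-years.
- VW discharge to last call: 200 × 84/365.25 = 46.0 patient-years.
- VW admission to last call: 14 + 84 = 98 days, or 200 × 98/365.25 = 53.7 patient-years.

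**3. Does the 3-month period settle the origin?** Three months is about 91 days. Counting from VW discharge gives 84 days (7 short). Counting from VW admission gives 98 days (7 over). Both fit equally well, so the origin stays open.

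**4. Share of events in the stay, and effect on a comparison.** Let k be the hazard during the stay divided by the hazard afterwards. The documents give no value, so k = 1 to 4 is an assumed range.
- Share of the 98-day events that fall in the stay = 14k/(14k + 84).
- Suppose the VW has no effect, the comparator is counted over all 98 days from the qualifying event, and VW admission falls on that day. The comparator's average hazard is (14k + 84)/98 times the later hazard. The VW rate counted from VW discharge equals the later hazard. Apparent rate ratio = 98/(14k + 84).

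| k | Share in stay | Apparent rate ratio |
|---|---|---|
| 1 | 14/98 = 14% | 98/98 = 1.00 |
| 2 | 28/112 = 25% | 98/112 = 0.88 |
| 3 | 42/126 = 33% | 98/126 = 0.78 |
| 4 | 56/140 = 40% | 98/140 = 0.70 |

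**5. Overlap with the window used for sizing.** The source rate covers the 2 weeks after hospital discharge. For patients who enter by that route, this is roughly the VW stay. Hospital discharge is one of four entry routes, and its share is not given. If 25%, 50%, 75% or 100% enter that way (assumption), those patients account for 9.5, 19, 28.5 or 38 scaled events. If VW admission lags hospital discharge by 0, 3 or 7 days (assumption), the overlap of the 2-week window with the stay is 14/14 = 100%, 11/14 = 79% or 7/14 = 50%.

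**The case against.** The strongest reply is that call dates are not a risk window. The abstract says when patients are telephoned, not that only later events count. A call 2 weeks after VW discharge can ask about earlier events. Recording is described as prospective, and clinicians speak to patients throughout the stay, so a re-hospitalization would be hard to miss. The key sentence comes from an abstract, counting rules are often left to a full protocol or SAP, and the design flow diagram (Figure 1) is not shown. The primary outcome is the number of care gaps and interventions, which does not depend on this clock.

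Much of this stands. A reader might infer that in-stay events are excluded, or that the rate is computed only in patients who complete the stay. The article says neither: no sentence drops a patient re-hospitalized during the stay or removes the event from the count. A reader might also infer that all of the planned 40 events lie in an omitted window. That does not follow. Those are adverse events of any kind rather than re-hospitalizations, they are scaled from patients leaving hospital (one entry route of four), and no omission is stated. The downward bias is conditional too, because the comparator's origin is not given and at k = 1 there is no bias.

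What the reply does not remove is that the article does state an origin for follow-up, and it is VW discharge. Its list of in-stay domains does not include the outcome. Asking about earlier events at a later call would still leave open whether the 14 days belong in the denominator. At constant hazard, counting in-stay events over only the 84 later days would inflate the rate by 98/84 = 1.17.

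**Conclusion.** The concern holds as a defect in how the risk window is fixed, not as a stated exclusion of events. The only dated schedule runs from a discretionary post-entry time, the 3-month period has no origin, and no rule covers events or person-time during the stay.

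Read literally, 14 of 98 days lie outside the stated ascertainment. The 14% share of events assumes constant hazard and a stay of exactly 14 days; the 25% to 40% range assumes k = 2 to 4. The spurious rate ratio of 0.88 to 0.70 further assumes a comparator counted from the qualifying event, no delay to VW admission, and no true effect. These figures illustrate what the open origin could do and do not estimate what will happen.

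The affected outcomes are secondary: re-hospitalization number and rate, the care gaps associated with it, service-use rates, and the before/after and matched-cohort comparisons. The point is worth correcting before those rates are computed, but it is not a must-fix for the primary outcome.

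**What to change.** State the following in the protocol:

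- Time zero for every re-hospitalization and utilization rate is VW admission, with a fixed end day that is the same for all patients. Day 90 is one example: the 12-week call reaches it for any stay of at least 90 − 84 = 6 days.
- Events and person-time during the stay count in the numerator and denominator. Add a short hospitalization and service-use item to the existing VW calls; the 2-, 4- and 12-week calls cover the rest.
- A re-hospitalization during the stay is an outcome of that VW admission. Re-entry to the VW neither restarts nor duplicates the patient's follow-up.
- The before/after and matched-cohort comparisons use the same origin as far as the data allow. Where they cannot, report the difference in origin with the result.

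The cost is protocol wording and slightly more data capture in calls that are already planned. No new patient contacts are needed.

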**Discussion:**

This report serves as a blueprint for the design and implementation of a novel health service delivery model for home dialysis patients. The major goal of the HDVW initiative is to provide appropriate and effective supports to medically complex patients in a targeted window of vulnerability.

**Trial registration:**

(NCT01912001).

## Background

Patients with end-stage renal disease (ESRD) have a high burden of co-morbidity. The most common renal replacement therapy (RRT) in North America is conventional, thrice weekly, in-center hemodialysis (CHD). Home dialysis modalities (peritoneal dialysis (PD) and home hemodialysis (HHD)) are comparably under-utilized, but RRT in the home setting offers greater quality of life [1,2], higher patient satisfaction [3,4] and several other clinical advantages, including better survival compared to CHD [5-10].

These clinical advantages coupled with greater cost-efficacy have made expansion of home dialysis programs a mandate for many healthcare providers [1,11]. Although factors influencing technique failure and recruitment challenges to home dialysis have been examined previously [12-14], the absolute growth of home dialysis remains modest. The underlying reasons for inflow and outflow of patients through home dialysis programs suggest a role for interventions, which may enhance benefits and allay concerns [15]. Conceptually, an innovative care model that provides support to patients would improve retention by decreasing preventable causes of attrition and might also enhance recruitment through improving quality of support of the chronically ill at home.

Periods of transition from acute care to other settings are thought to represent a window of exaggerated patient vulnerability [16,17]. This is because several aspects of the care plan for complex patients may have changed during hospitalization [18,19]. Multiple categories of risk are prevalent during such transitions. These include changes in medication type, dosing and interaction issues, susceptibility to nosocomial infections, confusion regarding follow up, and failure to communicate with primary care providers. This subtlety is not lost on dialysis patients, who rate coordination of care between nephrologists and other physicians lower than other domains of patient satisfaction [3].

Meeting the logistical challenges of improving transitions hinges critically on optimizing clear and timely communication. Thus, care models, which utilize the specialized knowledge of physicians to enhance communication within the healthcare team, are likely to be beneficial. Virtual wards (VW) are a new model of integrated care that seeks to leverage the infrastructure, “systems, staffing and daily routines of a hospital ward…”, to provide services to patients who are not physically admitted to hospital [20]. We have developed a VW model that will capitalize on the infrastructure built for the running of a home dialysis program (PD and HHD). We envisage this VW to function as a pro-active, systematic management tool for vulnerable patients. We hypothesize that implementation of the VW will mitigate gaps in care that occur following care transitions and will facilitate a supported return to baseline health status.

### Objectives

The home dialysis virtual ward will aim to enhance patient care in the following domains:

1. Dialysis prescription and adherence.

2. Morbidity associated with dialysis therapy.

3. Burden associated with travel time for patients.

4. Medication reconciliation.

5. Symptom management.

6. Coordination of care among participating providers.

7. Patient satisfaction.

## Methods/design

### The virtual ward intervention

The home dialysis VW protocol, tools, and evaluation system was developed through an adaptive design process. The members of the VW design team include a physician, pharmacist, dietician, home dialysis nurse, and social worker. Our protocol has been approved by research ethics board (UHN: 12-5397-AE). Written informed consent for participation in the study will be obtained from participants.

The VW intervention consists of a scheduled once to thrice - weekly physician or nurse telephone-administered standardized patient assessment tool. This tool was developed through iterative steps based on input from nephrologists (MS and CC), home dialysis nurses, and renal dieticians. The tool was vetted through dedicated nephrology divisional rounds at the University of Toronto. Feedback from academic nephrologists as well as allied health care staff was incorporated into the final version.

The standardized patient assessment tool serves as a data collection, and clinical form. Relevant domains are identified including: 1. Indication for admission to the VW; 2. Dialysis prescription; 3. Demographic and comorbidity data; 4. Medication reconciliation and 5. Symptom assessment.

The VW nephrologist admits patients and administers the standardized patient assessment tool over the telephone during scheduled VW appointments. Subsequent use of the tool proceeds 1–3 times per week by a member of the team. Patients are admitted to the VW for a planned duration of 14 days and discharged at the discretion of the health team.

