Improved symptom management has the potential to minimize patient-morbidity and may reduce un-scheduled health-system utilization such as emergency room or walk-in clinic visits. Our intervention specifically targets serial measurement of symptoms score which will allow early identification and optimization of symptoms. Similarly, timely changes in dialysis prescription may decrease the likelihood for extra-cellular fluid overload, which may prevent future hospitalization. Finally, adjustment of medications to reflect evidence-based practice or to minimize risks of drug-interactions is of clear benefit.

While the HDVW may serve to improve patient care, it is equally important to balance the utility of any intervention with its intrusiveness. Patients’ perceptions and satisfaction with the VW service will therefore be analyzed. Patient satisfaction is recognized as an important clinical outcome, which will also provide us an important quality performance measure [27,28].

Implementation of the HDVW strategy will undoubtedly change work flow within the clinical team. It will therefore be important to quantify the amount of time each VW ward admission will require. It is reasonable to speculate that if our present care model is deemed successful, regionalization may ultimately prove to be the most cost efficient approach to broadening availability of this health service offering.

Although the VW model proposed herein does not require additional infrastructure, it is important to recognize potential barriers to its implementation. As a result, we elected to conduct our study in a Vanguard fashion so that a proof of concept feasibility demonstration could be achieved. We envision that our strategy will be cost-neutral, while providing a patient centered sub-specialist delivery service.

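### Symptom change is scored at virtual-ward discharge, a day chosen by the team that sees the scores; scoring every patient at day 14 removes a small, avoidable timing bias

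*Protocol article*

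**What the plan says.** All references are to the protocol article.

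- **Outcome.** Under Secondary outcomes, the first item is "Within subject differences in symptoms score at baseline and at discharge of VW".
- **Length of stay.** Under The virtual ward intervention: "Patients are admitted to the VW for a planned duration of 14 days and discharged at the discretion of the health team". No discharge criterion or maximum stay is given.
- **Who scores.** The same section says of entry: "The VW nephrologist admits patients and administers the standardized patient assessment tool over the telephone during scheduled VW appointments". For later contacts: "Subsequent use of the tool proceeds 1–3 times per week by a member of the team". Symptom assessment is one domain of that tool, which doubles as the clinical form, so the team knows the running score.
- **What the scores are for.** The Discussion says: "Our intervention specifically targets serial measurement of symptoms score which will allow early identification and optimization of symptoms". The Background hypothesizes that the ward "will facilitate a supported return to baseline health status".
- **Abstract.** The schedule is summarized as "Clinician-led telephone interviews are performed weekly for 2 weeks until VW discharge", which suggests a fixed stay. Adverse events and service use are then collected by "telephone follow-up after discharge from the VW at 2, 4, 12 weeks".
- **Comparators.** The matched cohort and the before-and-after comparison described under Secondary outcomes concern hospitalization, not symptoms.

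**The concern.** A before-and-after measure needs a second time point that does not depend on the measurement. Here the second time point is an event, discharge, decided by people who hold the current score. If a patient who still scores high at day 14 is kept until a later call gives a lower score, the recorded change includes favorable chance fluctuation. It also covers a longer recovery period than another patient's change does. With no control group for symptoms, nothing offsets either effect.

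This is not a detail left to an unseen analysis plan. The article fixes the time point, and fixes it to an event that can depend on the outcome. Symptom management is one of the listed objectives.

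**Working it through.** **The plan's own figure.** The only sizing figure is the expected number of adverse events under Implementation: 200 × 76/400 = 38, which the article rounds up to at least 40 because its patients are more complex. It reproduces, but it does not bear on the symptom score. No SD, correlation or discharge pattern is given, so everything below is assumption and range.

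**Model.** The unit is the SD of one reading around the patient's own level; a stable personal level cancels in the difference. Assumed rule: a patient not below the entry score at day 14 stays, leaves at the first lower reading, and leaves at day 21 at the latest. There is no true change. Let k be the number of eligible readings: k = 1 for a fixed day 14, k = 2 for weekly calls (days 14, 21), k = 4 for three calls a week (days 14, 17, 19, 21).

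**Step 1: independent readings.** With entry score X0, p = Φ(X0) and φ the normal density,

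mean spurious improvement = E[ (1 − (1 − p)^(k−1)) · φ(X0)/p ].

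- k = 1: 0.
- k = 2: E[φ(X0)] = 1/(2√π) = 0.28.
- k = 4: 0.51 (numerical integration; simulation agrees).

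**Step 2: correlated readings.** Simulation with correlation decaying over time, every admission timed by the rule:

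| 7-day correlation | Weekly calls | Three calls a week |
|---|---|---|
| 0 | 0.28 | 0.51 |
| 0.5 | 0.12 | 0.14 |
| 0.7 | 0.06 | 0.07 |
| 0.8 | 0.03 | 0.04 |

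Scoring at day 14 gives 0.00 in every row.

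**Step 3: only a share of admissions timed this way.** The bias scales with the share. At correlation 0.5 and a 25% share it is 0.25 × 0.12 = 0.03 (weekly) or 0.25 × 0.14 = 0.035 (three a week). The correlation between day 0 and day 14 is 0.5² = 0.25, so the SD of the change is √(2 × 0.75) = 1.22. With n = 200 the standard error is 1.22/√200 = 0.087. The bias is therefore 0.35 to 0.40 standard errors. An assumed two-sided 5% paired test would then reject in about 6.4% to 6.9% of trials, and simulation gives 6% to 7%. At a 50% share the bias is 0.06 to 0.07 SD and rejection is about 10% to 13%.

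**Step 4: true recovery present.** With recovery of 0.5 to 1.0 SD by day 14 and correlation 0 or 0.5, late discharge under the same rule overstates the day-14 change by 0.10 to 0.50 SD when every admission follows it.

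**Step 5: early discharge.** If discretion is used instead to release patients from day 7 once they score lower, with recovery of 0 to 1.0 SD by day 14, the error against the day-14 change runs from −0.30 to +0.51 SD. Early exit picks favorable readings but also cuts recovery short.

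**The case against.** The strongest reply is that the harm depends on conduct the article does not describe. It plans 14 days, the abstract speaks of two weeks, and nowhere does it say that symptom scores govern discharge. That stands. Discretion permits score-driven timing but does not establish it, and if everyone leaves on day 14 there is no distortion. The two-week wording does not settle the matter, though: it neither withdraws the discretion nor moves the outcome off discharge.

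A reader might go further in four ways that the documents do not support.

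- *The team keeps patients until their scores look good.* No such motive or rule is stated. Patients rate their own symptoms, and acting on scores is described as care.
- *The improvement is always overstated.* That holds for late discharge under the rules tried; early discharge can bias either way.
- *The bias is 0.28 to 0.51 SD with a badly inflated error rate.* Those figures need independent readings and every admission timed by the score. A different assumed rule, holding patients above a fixed cut-off past day 14, gives 0.05 to 0.30 SD (of the total score) and rejection rates of 19% to 99% at n = 200. It applies to the whole cohort, in some settings to day 28, and nothing in the article supports departures on that scale.
- *A false-positive rate is the natural yardstick.* The article states no test for symptoms. Most entry criteria follow an admission, a procedure or an infection, so natural recovery alone could reject no change.

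It is also fair to say that entry-to-discharge change is a legitimate description of a care episode, and that a score near day 14 should already exist for patients still on the ward. Both argue for keeping the discharge score as description. Neither supplies a common time point for patients who leave early.

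**Conclusion.** The point holds as a minor one, for this secondary outcome only. The time point of the symptom outcome can depend on the symptom score, follow-up can be unequal, and no control group offsets either.

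The size is uncertain and probably small: zero if all leave at day 14; about 0.03 to 0.14 SD if every admission follows the assumed stay-until-lower rule to day 21 with no true change and 7-day correlations of 0.8 down to 0.5; about 0.03 SD, with 6% to 7% false positives, if a quarter do so at correlation 0.5 with 200 patients. The correlations, the rule, the share and the paired test are all assumptions.

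Fixing the day removes the timing bias in either direction. It does not remove natural recovery or regression to the mean, so the change still could not be attributed to the ward. No claim is made here about the primary outcome or the re-hospitalization comparisons.

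**What to change.** Redefine the first secondary outcome as the change in symptom score from VW entry to day 14 (±2 days) for every patient, whether discharged before, on or after that day. Report the discharge-day score and the length of stay descriptively. Leave the discharge decision with the team.

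The cost is one sentence in the outcome definition. Patients leaving on day 14 need nothing extra. Patients kept longer are called at least weekly, so one call can be placed on day 14. Early leavers need one short symptom call: if 10% to 25% of 200 left early (assumed), that is 20 to 50 calls. The existing post-discharge calls do not replace it, because they are timed from discharge; a patient discharged on day 7 gets the 2-week call on day 21. The downside is that the reported improvement may be smaller than at discharge.
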